**Figure 1 figure1:**
[figure not shown]
Trial design and timeline. DAF: Delayed Auditory Feedback; OASES: Overall Assessment of the Speaker’s Experience of Stuttering; SS%: percentage of stuttered syllables; SSI-4: Stuttering Severity Instrument-Fourth Edition; tDCS: transcranial direct current stimulation.

### Randomization and Blinding

This study is a randomized, double-blind, sham-controlled trial. Participants will be randomly allocated to the intervention and control groups. The random assignment of participants ensures the prevention of a possible selection bias and a disbalance of confounding factors between the study arms. Randomization will be performed via a web-based randomization tool [22]. In accordance with the requirements of this tool, we will include 50 subjects and 4 blocks of equal size, for which randomization will be performed independently. Each subject will be given an ID number and will be assigned to one of the treatment groups. The individual responsible for generating the random list will not be involved in any other part of the trial.

As the study is double-blinded, neither the participants nor the investigators will know which group each participant will be assigned to. Sealed opaque envelopes will be used for concealment. Accordingly, an envelope will be produced for each subject. These envelopes will be marked with an ID number, and the treatment group associated with each ID will be placed in its respective envelope. In order to guarantee double blinding, specific letters, unknown to the principal investigator and the subjects, will be used instead of the actual names of the treatment groups (ie, intervention and control) inside the envelopes. Assignment of these letters to the respective intervention group will be done by a clinician (not the principal investigator). Before the principal investigator starts the treatment of the respective participant, the subject will be given one of the sealed envelopes by the clinician. Once the envelope is opened by the corresponding participant, the clinician will set up the mode—anodal or sham—based on the content of the subject's envelope and attach the electrodes to the participant´s head as illustrated in the sections below. Once completed, the principal investigator will commence the treatment. The researchers who are responsible for outcome assessment and data analysis will also be blinded to the intervention groups.

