During the two baseline sessions, the principal investigator will observe physical behavior, which is required to calculate the SSI-4 score. The final part of the preintervention assessments is the completion of the OASES questionnaire by the participants. After the second baseline assessment, the intervention will start and carry on for 6 consecutive days.

At 3 time points after the last intervention session (ie, immediately, 1 week, and 6 weeks), each subject will undergo postintervention assessments, which will be identical to the preintervention assessments and obtained by the same raters. The trial design and timeline are shown in Figure 1.

After each intervention session, participants will fill out a questionnaire using a 5-point Likert scale (1=very mild, 5=very severe) to report potential side effects of tDCS, including itching, burning, tingling, headache, fatigue, sudden mood change, difficulties in concentration, changes in visual perception, unpleasant somatosensory sensations, unpleasant visual sensations, nausea, drowsiness, persisting feelings of stimulation, and 1 open question for any other adverse effects.

In addition, to ensure successful blinding, participants will be asked to guess the type of treatment they will or had received (ie, anodal tDCS or sham) before and after the intervention.

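### Allocation is coded by letters that stand for the group, and participants open the envelope holding their letter, so if one letter is decoded the exposure need not stop at one person

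*Protocol article*

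**What the plan says.** The procedure is in the protocol article under Randomization and Blinding. There is one sealed envelope per participant: "These envelopes will be marked with an ID number, and the treatment group associated with each ID will be placed in its respective envelope". Letters stand in for the group names; they "will be used instead of the actual names of the treatment groups (ie, intervention and control) inside the envelopes". The article describes them as "specific letters, unknown to the principal investigator and the subjects". A clinician other than the principal investigator decides which letter means which group, and this clinician also hands over the envelope. Then: "Once the envelope is opened by the corresponding participant, the clinician will set up the mode—anodal or sham—based on the content of the subject's envelope". The principal investigator begins treatment only after the clinician has finished the set-up.

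The stated aim is that "neither the participants nor the investigators will know which group each participant will be assigned to". For assessors and analysts: "The researchers who are responsible for outcome assessment and data analysis will also be blinded to the intervention groups".

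Study Design adds a second role for the person who runs the treatment: "During the two baseline sessions, the principal investigator will observe physical behavior, which is required to calculate the SSI-4 score". It also says that the assessments after treatment repeat those before treatment and use the same raters.

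**The concern.** Two features of the procedure weaken the blinding it is meant to protect.

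First, the code belongs to the group, not to the person. Participants in the same arm may therefore share a code, and whatever is learned about one of them carries over to the others with that code.

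Second, the participant opens the envelope and can read the letter. No purpose is given for this step, since the clinician already delivers the envelope, holds the key and sets the device. Nothing stated prevents a participant from repeating the letter to someone else.

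The outcomes most exposed are those that depend on a person's judgment. The principal investigator runs the treatment and also observes the physical behavior that enters the SSI-4 score. The OASES is completed by the participant. Either could shift if allocation became known. SS% is better protected: two raters count it independently from voice recordings, with a third for disagreements.

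**Working it through.** **Consistency of the text.** The letters are said to be unknown to the subjects, yet the subject opens the envelope containing the letter. There are two readings.

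- The letter itself is meant to be unknown. Then the opening step contradicts the description.
- Only the letter's meaning is meant to be unknown. Then the text is consistent, but all protection after opening rests on the key held by the clinician.

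Either way the sentence needs to be reworded.

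**How far one decoding could spread.** The protocol gives no figure for this, so there is none to reproduce. The inputs are:

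- 25 participants per group, 50 in total (Intended Sample Size);
- letters per arm, L: not stated, so varied here, with letters assumed to be spread evenly within an arm;
- the person who learns one letter's meaning also knows which letter each other participant holds: an assumption that gives the ceiling.

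Direct exposure from decoding one letter = 25 / L. When L = 1 there are only two letters, so the other letter is decoded by elimination and its 25 holders are added. When L is above 1, decoding one letter does not settle the rest.

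| Letters per arm | Direct | By elimination | Ceiling |
|---|---|---|---|
| 1 | 25 / 1 = 25 | 25 | 50 of 50 |
| 2 | 25 / 2 = 12.5 | none | 12 to 13 of 50 |
| 5 | 25 / 5 = 5 | none | 5 of 50 |
| Unique code per participant | 25 / 25 = 1 | none | 1 of 50 |

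One letter per arm is the natural reading of letters that replace two group names, but it remains an inference.

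**What has to happen first.** Three conditions must hold together: the meaning of a letter is disclosed or inferred; the person who learns it knows which participant or participants hold that letter; and the same person knows other participants' letters. The article states none of these. Inference is at least conceivable. Active stimulation lasts 20 minutes, while sham ramps down after 30 seconds, and participants report sensations such as tingling, itching and persisting feelings of stimulation after each of six sessions. Someone who knew the letters could compare those reports by letter even if no single report were decisive. Individual codes close that route.

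**Who is already unblinded.** The clinician sets anodal or sham and so must know the mode. Giving the opening of the envelope to this clinician unblinds no additional person.

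**The case against.** A reader might infer that one leaked letter unblinds a whole arm. The article does not support that. The letter is a symbol whose key stays with the clinician, so reading or repeating it tells nobody the mode.

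A reader might also infer that the principal investigator sees the letters and can sort participants by them. That is not stated either. The letters are described as unknown to the principal investigator, and the order of events has the clinician complete the set-up before the principal investigator begins. Knowledge could reach the principal investigator only if participants passed it on. Nor can skin damage that leads to withdrawal be taken to reveal the mode. The article does not say so, and sham delivers current at the same intensity before it ramps down.

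Three further defenses have weight. SS% comes from recordings, and assessors and analysts are stated to be blinded. Participants' guesses of their treatment are collected and tested, so failed blinding of participants could be detected. And a journal article may leave the handling of the slips, and the number of letters, to a fuller protocol.

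These points limit the concern but do not remove it. The guess test detects unblinding without preventing it, and it does not cover the principal investigator. The statement that assessors are blinded is an aim, and the group-level code gives it weaker support than it could have. The choice of code and the person who opens the envelope are not omitted detail: the article states both.

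**Conclusion.** The point holds as a conditional weakness of the blinding and a conflict in wording. It is not evidence that blinding was lost. If one letter is decoded, the ceiling is 50 of 50 participants with one letter per arm, about 12 to 13 with two and 5 with five, against 1 with individual codes. These are upper limits on exposure, not estimates of bias. They rest on an assumed number of letters and on other participants' letters being known to the person who learns the meaning. The outcomes mainly at risk are the SSI-4 physical-behavior score, observed by the person who runs the treatment, and the OASES. The change is worth making because it is nearly free and removes the inconsistency. No sample-size, alpha or power figure is affected.

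**What to change.** For participants not yet randomised, revise Randomization and Blinding as follows.

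- Replace the group letters with a unique code for each participant ID.
- Have the clinician who sets the device open the envelope, out of sight of the participant and the principal investigator, and keep both the envelope and the code list. The list should not go to the person who generated the randomization sequence, because the article gives that person no other part in the trial.
- Reword the statement about what is unknown, so that it says neither the code nor its meaning is available to the participant or the principal investigator.

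The article reports 30 participants enrolled by February 2020. Counted from that date, the change could cover at most 50 − 30 = 20 of the planned sample, so the figure of 1 in 50 is no longer attainable for the whole trial. For those already enrolled, restrict access to the opened envelopes.

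The cost is one code lookup per participant by the clinician. No staff or visits are added.

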### Intervention Program

#### Performance of Transcranial Current Direct Stimulation

The stimulation will be done by passing a current of 1 mA between two 5 cm × 7 cm electrodes for a duration of 20 minutes with ramp-up and ramp-down intervals of 15 seconds. This common setup has been shown to be efficient for enhancing speech fluency in previous tDCS studies [3,4]. A neuroConn DC-STIMULATOR will be used to deliver tDCS. The electrodes used for tDCS are conductive rubber electrodes encased in a sponge pocket, and saline solution will be used as an electrolyte-based contact medium. The electrode sponges must be saturated with saline. It is crucial that each side of the sponges is sufficiently moisturized, but not overly saturated, to avoid dripping. Before placing electrodes on the scalp, the clinician will inspect the skin for any skin damage or lesion. For both anodal and sham modes, the same stimulation intensity parameters will be used. However, for the sham stimulation, the device will ramp down automatically after 30 seconds. The intervention will be conducted for 6 consecutive days.

An electroencephalogram cap will be used to identify the site of stimulation. The anode electrode will be placed over the left superior temporal gyrus (T3 according to the 10-20 international system [23]), and the cathode electrode will be positioned over the right frontopolar region (Fp2 according to the 10-20 system [23]). To prevent movement of the electrodes, their positions will be fixed by elastic rubber straps. Electrode placement is shown in Figure 2.

**Figure 2 figure2:**
[figure not shown]
Electrode placement.

#### Performance of Delayed Auditory Feedback

During stimulation, participants of both groups will receive DAF as a fluency treatment. In order to deliver DAF, Audapter, which is a software package for manipulating the acoustic parameters of speech in real time, will be used [24]. This package consists of the core algorithm for real-time manipulation and a MATLAB wrap-around. The real-time signal processing algorithms are coded in C++. The subjects will perform 3 tasks (ie, oral reading, monologue, and conversation) with DAF <60 ms. This 60-ms delay has been shown to be efficient to enhance speech fluency in individuals with a stutter [25].

Although, as outlined above, we do not anticipate major adverse events, the occurrence of skin irritations, itching, tingling, burning, or pain (including headache) will be monitored. After each intervention session, a side effects questionnaire will be filled out by participants. Furthermore, participants will guess if they received anodal or sham stimulation before the intervention, after the first session, and after the intervention period to ensure successful blinding.

Data from the respective questionnaires will be recorded on paper, and recordings of subjects’ voices will be stored electronically. Access to data resources will be restricted to the investigators. Finally, all study documents will be securely maintained for 2 years.

### Statistical and Analytical Analyses

In this proposal, the null hypothesis (H_0_) is that the combined treatment method using tDCS stimulation and DAF, as compared to DAF combined with sham stimulation, has no additional effect on the enhancement of speech fluency in adults who stutter.

#### Intended Sample Size

Based on the previous study by Chester et al [4], and using G*Power software [26], 25 subjects per group (50 participants in total) are required to detect a significant difference for a time × group interaction using a two-way mixed model analysis of variance (ANOVA). Time is the within-subject factor (ie, before the intervention and immediately, 1 week, and 6 weeks after the intervention), and group is the between-subject factor (ie, anodal or sham tDCS). The dependent variable is stuttered syllables (SS%). Type I (α) and type II (β) errors are set at .05 and .20, respectively, and the effect size is 0.17.

#### Other Statistical Analyses

Descriptive statistics will be calculated for demographic and baseline characteristics as well as primary and secondary outcomes for all participants. For every subject, summary statistics including mean, SD, median, minimum, and maximum will be provided for quantitative variables. For qualitative variables, frequency tables will be presented. Group differences of demographic variables will be assessed by Student *t* tests for quantitative variables and chi-square tests for qualitative variables.

In order to evaluate the effect of the treatment, the early and late outcomes (ie, measurements taken immediately, 1 week after treatment, and 6 weeks after treatment) will be examined. Depending on the significance of the ANOVA results, exploratory post hoc Student *t* tests will be conducted to compare conditions. The same procedures will be conducted for the secondary outcome parameters.

Data on tolerability and safety will be analyzed using an independent samples *t* test for common adverse events. Reports of rare side effects will be documented. To confirm successful blinding, a chi-square test will be applied.

Participants may be lost to follow-up for two reasons: (1) they have not completed at least 80% of the treatment (5 out of 6 sessions) and (2) they did not show up for the outcome measurement sessions 1 week or 6 weeks after the intervention. In these cases, intention-to-treat and modified intention-to-treat approaches will be employed. For cases lost to follow-up, efforts will be made to identify the reason, for example, by phone.

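### A chi-square test with 25 per arm cannot confirm blinding: it usually misses moderate unblinding and cannot exclude serious unblinding, and two sections disagree on when guesses are taken

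*Protocol article*

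**What the plan says.** In the protocol article, the blinding analysis is one sentence under Other Statistical Analyses: "To confirm successful blinding, a chi-square test will be applied". It gives no threshold and no effect estimate, and does not say what result would count as confirmation.

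The guess has two options, anodal or sham. The timing is described twice:

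- Study Design: participants are asked to "guess the type of treatment they will or had received (ie, anodal tDCS or sham) before and after the intervention". That is two times.
- Performance of Delayed Auditory Feedback: the guesses are taken "before the intervention, after the first session, and after the intervention period to ensure successful blinding". That is three times.

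The numbers available for the test come from Intended Sample Size: "25 subjects per group (50 participants in total) are required to detect a significant difference for a time × group interaction". That calculation concerns the primary outcome. The article gives no power for the blinding test.

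**The concern.** A chi-square test of guess by arm has equal guessing as its null hypothesis. A significant result is evidence of unblinding. A non-significant result means only that unblinding was not shown. A test whose declared purpose is to confirm blinding therefore treats non-rejection as the proof, and how far that misleads depends on how large a gap the test can miss.

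Unblinding by sensation is plausible here. Sham current ramps down after 30 seconds, whereas active stimulation lasts 20 minutes, and itching, tingling and burning are expected and recorded. The OASES is completed by the participants themselves. A report that blinding was confirmed would lend the sham comparison more credibility than 50 guesses can support.

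The timing discrepancy affects which data exist. A first-session guess is less open to influence from perceived benefit than one taken after six sessions, and one of the two sections omits it.

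**Working it through.** **Inputs.** From the article: 25 per arm and two guess options. Assumed, because the article does not state them: two-sided alpha 0.05 for this test, and the guess rates.

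**The article's own figure.** The 25 per arm comes from the primary analysis, with f = 0.17, alpha .05, power .80, two groups and four measurements. Using λ = f²·N·m/(1−ρ), with ρ = 0.5 and full sphericity (both assumed), λ = 0.0289 × 50 × 4 / 0.5 = 11.56 on 3 and 144 degrees of freedom. Power is 0.814, and 50 is the smallest even N that reaches 0.80. The stated size reproduces under those assumptions (ρ = 0.3 would need 68, ρ = 0.8 would need 22). It was not chosen with the blinding test in mind.

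**Power of the blinding test.** Let p₁ and p₂ be the probabilities of guessing anodal in the anodal and sham arms. The gap is p₁ − p₂, and the overall share correct is (p₁ + 1 − p₂)/2. The normal approximation is

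Φ{ [|p₁−p₂|√n − 1.96√(2p̄(1−p̄))] / √(p₁(1−p₁)+p₂(1−p₂)) }.

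For 60% against 40%: (0.2 × 5 − 1.96 × 0.707)/0.693 = −0.56, so power is 0.29. For 70% against 30%: (0.4 × 5 − 1.386)/0.648 = 0.95, so power is 0.83.

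Enumerating both binomials exactly at n = 25 gives:

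| p₁ | p₂ | Gap (points) | Share correct | Pearson | Fisher |
|---|---|---|---|---|---|
| 60% | 40% | 20 | 60% | 0.34 | 0.24 |
| 70% | 50% | 20 | 60% | 0.33 | 0.23 |
| 75% | 50% | 25 | 62.5% | 0.48 | 0.36 |
| 65% | 35% | 30 | 65% | 0.62 | 0.51 |
| 80% | 50% | 30 | 65% | 0.64 | 0.51 |
| 70% | 30% | 40 | 70% | 0.86 | 0.78 |
| 75% | 25% | 50 | 75% | 0.97 | 0.95 |

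For symmetric guessing, the normal approximation reaches 50% power at a gap of about 28 points and 80% power at about 39 points. To have 80% power at 60% against 40% would take 97 per arm.

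**What a non-significant result leaves open.** Take 15/25 against 9/25:

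- χ² = 50 × (15×16 − 9×10)² / (25×25×24×26) = 2.88, p = 0.09.
- Gap = 0.60 − 0.36 = 0.24, with SE = √(0.24/25 + 0.2304/25) = 0.137.
- 95% interval: 0.24 ± 1.96 × 0.137, or about −3 to +51 points.

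One more anodal guess in the anodal arm (16/25 against 9/25) gives p = 0.048 and an interval of about +1 to +55 points. The two data sets say nearly the same thing, but the test puts them on opposite sides.

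**Precision of the alternative.** With two options, the arm-specific index is 2p − 1, where p is the share correct in that arm. At p = 0.5 its SE is 2√(0.25/25) = 0.20 and its 95% half-width is 1.96 × 0.20 = 0.39. On the share correct this is 50% ± 20 points, about 30% to 70%.

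**Timing.** Set side by side, the two sections agree on a guess before treatment and one after it. Only the section on delayed auditory feedback has a guess following session one.

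**The case against.** A reader might infer that the test would usually miss serious unblinding. The figures do not support that. Power is 0.64 at 80% against 50%, 0.86 at 70% against 30%, and 0.97 at 75% against 25%. Only gaps below roughly 28 points are missed more often than not.

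A reader might also infer that the article declares blinding proven whenever p exceeds .05. No such rule is written. It is implied by giving the test the purpose of confirming, since non-rejection is the only outcome that could serve that purpose. The general promise of frequency tables for qualitative variables would naturally cover guesses, but it does not name them and does not change the stated purpose.

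A guess made before stimulation might seem worthless. It cannot detect unblinding by sensation, but it records expectation, against which later guesses can be read.

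The consequences are limited. SS% is counted from recordings by two independent raters, outcome assessors and analysts are blinded, the OASES is secondary, and no efficacy analysis depends on the chi-square result. Which guess is tested is a detail commonly left to an analysis plan, so its absence is not held against the article. Two times in Study Design may be shorthand for three. An index with a half-width of 0.39 cannot establish blinding either.

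All of this stands. It limits the point to the stated purpose of the test and the mismatch in timing. It does not rescue the use of a significance test as confirmation.

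**Conclusion.** The point holds in a limited form. With 25 per arm, non-rejection cannot confirm blinding. The Pearson test misses a 20-point gap about two times in three, and Fisher's test about three times in four. A non-significant result can remain compatible with a gap of about 50 points. Gaps of 40 points or more are usually detected, with power of about 0.78 or higher at the symmetric rates shown.

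These figures rest on assumed guess rates, two-sided alpha 0.05 and complete data. With 20 evaluable per arm, Pearson power at 70% against 30% falls from 0.86 to 0.71; the article states no dropout rate.

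The two descriptions of the guess times differ and need reconciling. The matter is worth correcting, but it concerns a supporting analysis and leaves the primary sample size and primary analysis untouched.

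**What to change.** Replace the blinding sentence under Other Statistical Analyses with text to this effect: *Treatment guesses will be tabulated by arm at each time point. For each guess taken after stimulation has begun, the proportion correct, or an arm-specific blinding index, will be reported with a 95% confidence interval. The guess before the intervention will be reported as baseline expectation. The end-of-course guess will be interpreted with the caveat that perceived benefit may influence it.* A chi-square p-value may still be shown, but without the claim that it confirms blinding. Which post-stimulation guess carries most weight is debatable: the first-session guess is less affected by benefit but cannot show unblinding that builds over later sessions. Reporting both avoids the choice.

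Amend Study Design to the three-time schedule given under Performance of Delayed Auditory Feedback. Because 30 participants were already enrolled by February 2020, also state how many have a first-session guess.

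The cost is wording and a simple calculation, with no added participants or visits. The drawback is a weaker blinding claim, because the index intervals will be about ±0.39 per arm. That is the real precision of 25 guesses.

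### Non-adherence is classed as loss to follow-up, unranked ITT and modified ITT sets sit beside an ANOVA that needs complete data, and N = 50 leaves no margin for attrition

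*Protocol article*

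**What the plan says.** Other Statistical Analyses lists two ways of becoming lost to follow-up. One concerns treatment received: "they have not completed at least 80% of the treatment (5 out of 6 sessions"). The other is failing to attend the 1-week or the 6-week assessment. For both, the section continues: "In these cases, intention-to-treat and modified intention-to-treat approaches will be employed". It defines neither set and does not say which is primary.

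Intended Sample Size states that "25 subjects per group (50 participants in total) are required to detect a significant difference for a time × group interaction". The model it names for this test is a mixed ANOVA with time and group as its two factors. The within-subject factor has four levels: "Time is the within-subject factor (ie, before the intervention and immediately, 1 week, and 6 weeks after the intervention"). It adds: "Type I (α) and type II (β) errors are set at .05 and .20, respectively, and the effect size is 0.17". Randomization and Blinding then plans to include 50 people, the same number as the calculated requirement.

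**The concern.** Two different events share one label. Stopping treatment early concerns exposure; missing an assessment concerns data. A participant with four sessions who attends all three post-treatment assessments has a full set of outcomes and belongs in an ITT analysis with observed values. Calling that person lost to follow-up invites the trial team to stop assessing them, or to handle them as missing.

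The label could also act unevenly. Textbox 1 allows withdrawal for skin damage or major adverse effects of stimulation. Intervention Program gives 20 minutes of current in the active arm, while the sham ramps down after 30 seconds. Withdrawals before the fifth session could therefore be commoner in one arm. If those people then leave the analysis, the comparison is no longer the randomised one.

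The only model named for the primary outcome is a classical mixed ANOVA, which needs all four values from each person unless gaps are imputed. The section foresees that visits may be missed, but does not connect this to its ITT commitment. The sample size has no room for such losses if the analysis is on complete cases.

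**Working it through.** **The label against the schedule.** Five of six sessions is 5/6 = 83%, and four of six is 4/6 = 67%, so the 80% rule takes effect at four sessions or fewer. Study Design sets assessments immediately, 1 week and 6 weeks after the last session. Nothing there makes an assessment depend on the number of sessions completed. A person can therefore meet the first reason for loss and still have every outcome.

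**Reproducing the sample size.** Inputs from Intended Sample Size: f = 0.17, α = 0.05, power 0.80, k = 2 groups, m = 4 time points. Not stated, and assumed here: correlation between visits ρ = 0.5 and sphericity (ε = 1). For the time × group interaction:

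- λ = f² · N · m · ε / (1 − ρ)
- df1 = (k − 1)(m − 1)ε = 3
- df2 = (N − k)(m − 1)ε
- power = P(noncentral F > 95th percentile of the central F)

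At N = 50: λ = 0.0289 × 50 × 4 / 0.5 = 11.56 and df2 = 48 × 3 = 144, giving power 0.814. The smallest N reaching 0.80 is 49, or 50 with equal groups. The plan's figure is reproduced. Other numbers of time points at ρ = 0.5 do not reproduce it: three give 58 and five give 43.

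**Power if only complete cases are analysed** (ρ = 0.5, ε = 1):

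| Complete cases | λ | df2 | Power |
|---|---|---|---|
| 50 | 11.56 | 144 | 0.814 |
| 49 | 11.33 | 141 | 0.805 |
| 48 | 11.10 | 138 | 0.795 |
| 45 (10% lost) | 10.40 | 129 | 0.765 |
| 40 (20% lost) | 9.25 | 114 | 0.708 |

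Under these assumptions, the second incomplete participant takes power below 0.80.

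**An illustrative loss.** The article gives no rate. If each of the two visits it names as missable were missed independently by 5%, then 1 − 0.95² = 9.75% would lack at least one. That leaves 50 × 0.9025 ≈ 45 complete cases and power 0.765. If the same people tended to miss both visits, fewer cases would be lost.

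**Sensitivity to the unstated inputs.** At N = 50, λ = 5.78 / (1 − ρ):

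- ρ = 0.3: λ = 8.26, power 0.656, required N 68.
- ρ = 0.7: λ = 19.27, power 0.966, required N 30. With 40 complete cases, power is still 0.915.
- ρ = 0.5 with ε = 0.9: power 0.781.

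The correlation matters more than the loss of a few participants. But only a value near 0.5 makes 50 the number required.

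**The case against.** The strongest reply is that the article never says under-treated participants are excluded. Its next sentence commits to ITT, so they are kept in at least one analysis. That stands. A reader might infer that ITT cannot be delivered, but it can be, with imputation or a likelihood-based model. Complete-case analysis is the usual behaviour of the classical method, not something the text states. The missing-data method and the definition of modified ITT may sit in an analysis plan or full protocol that is not shown, so their absence alone is no error.

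A reader might also infer that one population will be chosen once results are known. The text says both will be used. What it leaves open is which one carries the conclusion.

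A third tempting inference is that the stated 80% power is false. The calculation reproduces, and any shortfall depends on an unstated correlation, an assumed loss rate and complete-case handling. Nor does the session rule itself cost power. Power falls only if those participants' outcomes are missing or set aside.

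Two things survive because they are in the text: adherence is written into the definition of loss to follow-up, and the number to be included equals the number required.

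**Conclusion.** The point holds in a limited form. The article conflates non-adherence with loss to follow-up. It names two analysis sets without ranking them, beside an ANOVA that needs complete rows unless values are imputed. If that ANOVA is run on complete cases, the analysed set is not the ITT set, and post-randomisation exclusions could differ by arm. The documents do not show that this will happen.

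On size, 50 leaves a margin of one participant under the assumptions that reproduce it (ρ = 0.5, ε = 1, complete cases). A 10% loss would cost about 0.05 of power (0.814 to 0.765) and a 20% loss about 0.11 (0.814 to 0.708). These figures are conditional. With ρ = 0.7 the trial would tolerate a 20% loss easily; with ρ = 0.3 it would be short of 0.80 with no loss at all.

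**What to change.** 1. In Other Statistical Analyses, call fewer than five sessions non-adherence and keep loss to follow-up for missing outcomes. Invite non-adherent participants to the assessments already scheduled, unless they have withdrawn from these as well.
2. Make the primary analysis all randomised participants by assigned arm, in a likelihood-based mixed model for repeated measures that uses every available visit. Define the modified ITT set as those with five or more sessions and use it as a sensitivity analysis only.
3. In Intended Sample Size, state the correlation assumed. Say that 80% power presumes essentially complete data on 50 participants, and show power over a range of loss. The complete-case figures above can serve as a cautious guide; the mixed model keeps partial records and should lose less.

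The cost is mainly wording, plus the effort of bringing non-adherent participants back to existing visits. The article reports 30 enrolled as of February 2020, so at that date the change could still be made before analysis. There are two downsides: the estimate will include partially treated participants, and the stated power may look slightly less favourable.
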